### Eligibility criteria {10}

Eligible are patients aged 18–75 years with a chronic non-malignant pain condition as defined by the International Association for the Study of Pain (IASP) [59], and who meet the DSM-5 criteria for comorbid insomnia [1] determined by the Duke structured clinical interview [60, 61].

Exclusion criteria are (1) a comorbid drug abuse diagnosis, (2) involvement in ongoing compensation and/or insurance cases related to their current or previous health or treatment, (3) a current medical treatment using over 100 mg oral morphine equivalents, (4) a current involvement in other psychological treatments for pain and/or insomnia, (5) admittance to hospital psychiatric treatment during the past 12 months, (6) an epilepsy diagnosis, (7) poor Norwegian communication skills or (8) suffering from restless legs or sleep apnoea.

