### Outcomes {12}

The overall hypothesis is that the SleepWell intervention will outperform TAU. This will be tested using the following primary (A) and secondary (B) outcome measures:

(A)Favourable changes in the DSM-5 insomnia criteria (1) related to nocturnal symptoms (i.e. SOL-sleep onset latency, WASO-wake after sleep onset, EMA-early morning awakening) and daytime functioning (e.g. reduced dissatisfaction with nighttime sleep and fewer functional problems in education, work or social life). This is assessed with different classes of insomnia measures, i.e. the semi-structured Duke clinical interview for insomnia [60, 61], and the DSM-5 adapted Bergen Insomnia Scale (BIS) [67]. Comparable nocturnal improvements in SOL, WASO and EMA are registered across 7 days using an actigraphy recording device, while the sleep diary complements the actigraphy data. The clinical assessment process for diagnosing insomnia is primarily based on patients’ subjective reports. Thus, the SleepWell intervention will be considered efficacious if it results in a significant reduction in self-reported insomnia symptoms, as measured by the BIS, or in the proportion of individuals who satisfy the criteria for an insomnia diagnosis. Concomitant reductions in nocturnal sleep symptoms, as measured with the actigraphy/sleep diary, will broaden the support of the SleepWell.

(B)Improvements in objectively measured sleep with the “Home Sleep Test” device in terms of an increased proportion and duration of slow-wave sleep, reduced sleep fragmentation and fewer sleep disruptions due to EEG-based microarousals. Secondary measures also include reductions in patient-reported depression and anxiety, pain intensity and interference, fatigue and use of sleep medication, and improvements in pain acceptance and quality of life.

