### Sample size {14}

A meta-analysis of comparable somatic diagnoses (5 studies) indicated a standardised mean difference (Cohen’s *d*) between intervention and control ranging between 0.60 and 0.80 [18]. With randomisation done on an individual level, a correlation = 0.5 between pre- and post-test (R-sq = 25%), alpha = 0.05, power = 0.80 and minimum Cohen’s *d* = 0.60, at least *N* = 68 patients are required to reject the null hypothesis. With an estimated intra-class correlation (ICC) = 0.05 (adjustment for similarities that occur between patients due to sharing of a treatment group, cluster size = 6), which yields a design effect of 1.25 (1 + (6–1)*ICC), at least *N* = 85 participants are needed. Adding a safety margin of 20% dropout means a final sample estimate of *N* = 106 patients (*n* = 53 SleepWell, and *n* = 53 TAU).

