## Methods: data collection, management, and analysis

### Plans for assessment and collection of outcomes {18a}

The *primary outcomes* are measured by the following insomnia indicators:The Duke semi-structured clinical interview for deciding the presence of DSM-5 insomnia criteria [60, 61], and the Bergen Insomnia Scale (Five self-report items) for quantifying the dimensional level of DSM-5 insomnia nocturnal symptoms (sleep onset, maintenance and early awakening) and daytime consequences (poorer function in work, school or social life) that have lasted ≥ 3 months and occurred ≥ 3 nights a week [67]. The Duke interview also probes for other sleep disorders regarding patient exclusion, notably restless legs or sleep apnoea.Actigraphy (Actiwatch Spectrum Plus, Phillips Respironics) worn on the non-dominant arm, providing estimates of physical activity level, light exposure, SOL, duration of wake time during the nights, WASO and EMA. In addition, sleep continuity is calculated as the proportion of time in bed spent sleeping (SE %: sleep efficiency). Recordings will be performed for 7 days, and an average of the sleep indices will be calculated.The sleep diary will be manually completed every morning concerning the last night’s sleep and every evening concerning daytime fatigue or sleepiness. The diary will be used to complement the scoring of the actigraphy recordings.The *secondary outcomes* are measured by the following:A simplified PSG, i.e. the Home Sleep Test REM + (HST) (Somnomedics Randersacker Germany, GmhB), is used to complement actigraphy with sleep architecture assessments at nights 1–3 and REM sleep, arousals and sleep stage shifts. The HST can be used at home, allowing patients to hook up the equipment themselves. The device records 11 signals (3 frontopolar, 2 EOG, 1 EMG, snoring (sound), light in the room, movement, head position, continuous impedance measurement (signal quality), finger plethysmograph with oxygen saturation, heart rate and movement). We will evaluate whether patients receiving the SleepWell intervention attain a higher proportion or longer duration of slow-wave (N3) than light-wave (N1, N2) sleep than TAU patients and whether they attain a reduction in the arousal index or sleep stage index indicative of sleep disturbance. The recording will be made two nights per patient due to the “first night effect” related to habituation [68]. However, since the HST is less intrusive to wear and sleep with at home than a full PSG, the average of both nights will be used.The Hospital Anxiety and Depression Scale (HADS, 14 items) is designed for hospital populations as it rates the degree of non-vegetative symptoms of depression (7 items) and anxiety (7 items). Item scores range from 0 to 3, and total scores range from 0 to 21 for each subscale [69]. It is widely used as a screening instrument, and a HADS score ≥ 8 is used as a diagnostic marker [70] in Norway.The EQ-5Q-5L is a broad quality-of-life index covering the domains of mobility, self-care ability, daily activity function, pain/discomfort and affective symptoms [71].The Chalder Fatigue Scale (11 items) measures the degree of physical (7 items) and mental exhaustion (4 items) [72]. Each item is scored from 0 to 3 (total range, 0–33), with higher scores indicating more fatigue.The Brief Pain Inventory (BPI, 11 items) indexes pain intensity and interference, as well as body localisation of pain [73].

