### Statistical methods for primary and secondary outcomes {20a}

Patients randomly assigned to the waiting list (WL) group will conduct two baseline measurements separated by ~ 4 months, with the second one serving as the comparator to the post-test for the SleepWell groups. WL patients then cross over to the SleepWell intervention (Fig. 1) and follow the same plan for post-test and follow-up measurements as the SleepWell study arm.

The primary hypothesis examines the mean group difference between the SleepWell post-test status for all patients receiving treatment and the second baseline status of the WL patients having only received TAU. Since this test involves only two repeated measurements, a conventional analysis of covariance is used with the baseline value of the outcome added as a covariate. Designating baseline values as covariates has become standard practice in therapy research as it improves the precision of the mean difference estimate [80], which also improves the statistical power [81] in estimating the hypothesised mean group difference (0-SleepWell, 1-TAU).

Generalised linear mixed regression models are preferred due to the flexibility in managing most variables (continuous, binary, counts, etc.) and data clustering. Here, some degree of clustering may occur between individuals in the same therapy group as they share a common therapy climate (fellow group patients and therapists), which may underestimate the standard errors and increase the risk of a type 1 error in hypothesis testing. The effect of this nesting will be managed by adding the group number as a random factor.

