The GenLinMixed models for the later follow-up tests are comparable, except they add a random intercept factor in addition to the baseline adjustment to account for any leftover correlations in the repeated data, which adjusts the error bands appropriately. Because all patients have received treatment at follow-up, direct testing of general treatment–control effects at follow-up is irrelevant (the *Group* factor). The estimable fixed factors thus become *Time* (1-post, 2-follow-up at 4 months and 3-follow-up at 12 months) and the *Time*Group* interaction that allows mean group differences at different time points. We will analyse if relapse occurs during the follow-up period by conducting repeated time series contrast analyses. In case of significant contrasts indicative of relapse, we will examine for possible differences between the SleepWell (early treatment) and the TAU (late treatment) study arms. Effect size statistics will be given as a standardised mean difference by dividing the beta-weight for a group comparison or a time difference with the within-subject standard deviation for the test, i.e. the residual SD.

The analyses will be conducted conservatively as intention-to-treat. Alpha values < 0.05 and 0.01 are assumed for the hypotheses about primary sleep treatment outcomes, i.e. SOL, WASO, SE and EMA, and secondary outcomes, i.e. affective health, fatigue and quality of life, respectively. The alpha value is set to 0.01 for analyses of moderators and mediators. The GenLinMixed handles missing data adequately without the need for multiple imputations, as it estimates the parameters based on all data available [82], thus reducing biases related to dropout given a missing-at-random (MAR) dropout pattern.

Since moderator variables in CBT-i are imperfectly understood [83], exploratory moderator analysis will extend the above regression models by adding the moderator variable with its two-way interactions with Time and Group to get a full three-way interaction that may discern exactly the subgroups defined by the moderator that benefit the most from treatment.

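### The efficacy claim can be won on the BIS or on the insomnia diagnosis without an order or alpha split, and the protocol's lists of primary outcomes do not match

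*Protocol article*

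**What the plan says.** Four places in the protocol article bear on which result decides the trial.

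- **Outcomes {12}** sets the success rule, under which a significant decrease must be shown "in self-reported insomnia symptoms, as measured by the BIS, or in the proportion of individuals who satisfy the criteria for an insomnia diagnosis". It then gives the device and diary measures a lesser role: "Concomitant reductions in nocturnal sleep symptoms, as measured with the actigraphy/sleep diary, will broaden the support of the SleepWell".
- **Plans for assessment and collection of outcomes {18a}** opens its list with "The *primary outcomes* are measured by the following insomnia indicators". Under that line stand the Duke interview, the BIS, actigraphy (SOL, WASO, EMA and sleep efficiency) and the sleep diary.
- **Statistical methods {20a}** fixes the error levels: "Alpha values < 0.05 and 0.01 are assumed for the hypotheses about primary sleep treatment outcomes, i.e. SOL, WASO, SE and EMA". The 0.01 level goes to secondary outcomes, and also to moderators and mediators. Neither the BIS nor the insomnia diagnosis is named at either level.
- **Sample size {14}** is a single calculation for one standardised mean difference, with "alpha = 0.05, power = 0.80". It does not name the outcome.

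On adjustment, {20a} says that "a conventional analysis of covariance is used with the baseline value of the outcome added as a covariate". Eligibility {10} admits only patients "who meet the DSM-5 criteria for comorbid insomnia", as determined by the Duke interview.

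**The concern.** An either/or rule gives two chances at one claim. Unless the tests are ordered or alpha is divided, the chance of a false claim exceeds what a single test at the stated level allows.

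The section that assigns alpha also lists different outcomes from those that the success rule names. The two measures that can establish efficacy have no alpha level. Measures that can only add support are called primary and do have one.

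This could matter in practice. Study objectives {7} predicts larger benefits in self-reported than in objectively measured sleep. A clear BIS result beside null actigraphy is therefore a foreseeable outcome. It would count as efficacy under {12}, yet a report built on the {20a} list, if that list is read as actigraphy, could show no significant primary outcome.

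**Working it through.** **1. Reproduce the sample size.** Inputs from {14}: d = 0.60, pre-post correlation 0.5 (R² = 0.25), alpha 0.05, power 0.80, ICC 0.05, cluster size 6, dropout 20%.

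- Residual SD = √(1 − 0.25) = 0.866.
- Normal approximation, two-sided: n per arm = 2 × (1.960 + 0.842)² × 0.75 / 0.60² = 32.7, so 33 per arm and 66 in total. The noncentral t version gives 34 per arm, 68 in total, which is the stated figure.
- A one-sided test would need only 52 to 54 in total, so the plan is two-sided.
- Design effect = 1 + 5 × 0.05 = 1.25, and 68 × 1.25 = 85.
- 85 / 0.80 = 106.25, stated as 106.

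The figure reproduces, and it buys 80% power for one continuous comparison at two-sided 0.05.

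**2. Error rate of the either/or rule.** Assumption A: each route is tested two-sided at 0.05, the only level given for primary outcomes. Assumption B: the correlation between the two test statistics lies between 0 and 0.9, because the protocol gives none.

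If the tests are independent:

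- favourable direction only: 1 − 0.975² = 4.9%
- either direction: 1 − 0.95² = 9.75%

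For correlated normal test statistics, by simulation with 2,000,000 draws:

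| Assumed correlation | False claim of benefit | Any false-positive result |
|---|---|---|
| 0 | 4.9% | 9.75% |
| 0.5 | 4.6% | 9.1% |
| 0.7 | 4.2% | 8.4% |
| 0.9 | 3.5% | 7.0% |
| One test only | 2.5% | 5.0% |

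Only a reduction counts as success under {12}, so the middle column describes the rule as written. The excess is 3.5/2.5 = 1.4 to 4.9/2.5 = 2.0 times what one test allows.

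**3. Cost of splitting alpha.** At 0.025 per measure the independent-case error in either direction is 1 − 0.975² = 4.9%. With the same inputs, N rises from 68 to 82; 82 × 1.25 = 102.5, so 103; 103 / 0.80 = 128.75, so 129. At the planned size (85 / 1.25 = 68 effective, 34 per arm), power on one measure falls from about 80% to about 71% (noncentral t; 73% by the normal approximation).

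**4. Side-by-side reading of the lists.**

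| Measure | {12} success rule | {18a} | {20a} at 0.05 |
|---|---|---|---|
| BIS | decides | primary | not named |
| Duke diagnosis | decides | primary | not named |
| SOL, WASO, EMA by actigraphy/diary | supportive | primary | named, source not given |
| SE | not listed | primary (actigraphy) | named |

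**5. Baseline covariate for the diagnosis.** Every patient has the diagnosis at entry, so its baseline value is constant and explains no variation in the outcome.

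**The case against.** Much can be said for the plan.

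- **It never claims family-wise control.** Section {20a} sets levels for classes of hypotheses, and only a reduction counts as efficacy. A reader might infer that the stated 5% is broken. For false claims of benefit it is not: that rate stays just under 5%. What stands is that it exceeds the 2.5% that one two-sided test gives.
- **Six primary tests is not the rule.** A reader might add the two lists together and arrive at an error of 20.7% (correlation 0.5) to 26.5% (independent). The documents do not support this, because {12} lets actigraphy and diary results add support but not establish efficacy. The conflict in {18a} and {20a} is one of labels and alpha.
- **SOL, WASO and EMA are not foreign to the rule.** Section {12} presents them as nocturnal symptoms that the Duke interview and the BIS assess, and {20a} does not tie its list to a device. This softens the mismatch but does not remove it: SE is absent from the outcome list in {12} and is defined as an outcome only under actigraphy in {18a}.
- **The diagnosis can be analysed.** A reader might infer that the covariate rule makes this impossible. A constant baseline is merely uninformative, the unadjusted comparison remains valid, and {20a} already allows models for binary outcomes.
- **An analysis plan not shown might set a hierarchy.** It might. But the either/or rule and the mismatched lists are stated in this article, so they are conflicts in its text and not detail left for later.

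**Conclusion.** The point holds as an unordered either/or success rule together with primary outcome lists in {12}, {18a} and {20a} that do not agree. If each route is tested two-sided at 0.05, a false efficacy claim has probability 3.5% to 4.9% instead of 2.5%; counting both directions, 7.0% to 9.75% instead of 5%. These sizes rest on two assumptions: the 0.05 per route is inferred, since {12} says only that the reduction must be significant, and the correlation range of 0 to 0.9 is not from the documents. The mismatch of the lists depends on neither. It needs correcting because the confirmatory claim has no single deciding test, while the sample size pays for one. The numerical excess is moderate and is the lesser part of the point. The uninformative baseline diagnosis is a side matter.

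**What to change.** 1. In {12}, name one primary test: BIS at week 16, SleepWell versus TAU, two-sided 0.05. It is the only continuous measure in the efficacy rule and so fits a calculation based on a standardised mean difference, although {14} should say so by naming it.
2. Test the Duke diagnosis next, at 0.05, only if the BIS is significant.
3. Label SOL, WASO, EMA and SE from actigraphy and diary as supportive in {18a} and {20a}, and let {20a} assign its alpha to the BIS and then the diagnosis.
4. For the diagnosis, use the binary model that {20a} already allows, with baseline BIS as the covariate in place of baseline diagnosis.

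**Cost.** This is a change of wording, to be made before the analysts' masking under {17a} is lifted. N stays at 106. The small downside is that success on the diagnosis alone no longer counts. If both routes must be kept, alpha has to be divided: at 0.025, power on one measure falls to about 71%, or N rises to about 129. A Holm procedure meets the same loss whenever a measure has to be tested at 0.025.

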### Participant timeline {13}

The timeline for participant recruitment, intervention delivery and assessments is outlined in Figs. 1 and 2. After initial screening and confirmation of eligibility, participants will complete baseline assessments before randomisation. The intervention group will begin the SleepWell programme immediately, while the comparison group will continue TAU. Assessments will occur at the following intervals:Baseline (Week 0): Comprehensive evaluations using the Duke sleep interview for insomnia, sleep diaries, actigraphy, PSG/Home Sleep Test REM and self-report psychological instruments related to primary and secondary outcome variables, including mediation variables.Post-Intervention (Week 16): Assessment of short-term outcomes in SleepWell group, and second baseline measurement of the TAU group. The measurements are similar to those collected at baseline (week 0), in addition to qualitative interviews with the participants’ experiences of receiving the intervention.Post-Intervention for TAU (Week 32): This assessment is conducted after the TAU group has received the SleepWell intervention. The assessments are similar to those used at the post-intervention at week 16.Follow-Up Assessments: These are conducted 4 and 12 months after the post-test to evaluate maintenance of treatment effects. This is planned for weeks 32 and 64 in the SleepWell study arm and weeks 48 and 80 in the TAU arm. Self-report data are collected at the first follow-up test. At the final follow-up, both self-report data and actigraphy data are collected.

**Fig. 1 Fig1:**
[figure not shown]
Depiction of study design and timing of assessments. *D*-*interview* Duke diagnostic insomnia interview, *Q*-*interview* Qualitative interviews. Survey = Questionnaire outcome and mediation data according to section *Plans for assessment and collection of outcomes* {18a}. *PSG*/*HST* Polysomnographic Home Sleep Test with EEG-based registering of brain activity during sleep

**Fig. 2 Fig2:**
[figure not shown]
Schedule of enrolment, interventions and assessments. *SW* SleepWell intervention group, *C* control, wait-list group

Participants in the TAU arm will cross over to the SleepWell programme approximately 4 months after the baseline, ensuring access to the intervention while preserving the integrity of the initial randomisation.

### Sample size {14}

A meta-analysis of comparable somatic diagnoses (5 studies) indicated a standardised mean difference (Cohen’s *d*) between intervention and control ranging between 0.60 and 0.80 [18]. With randomisation done on an individual level, a correlation = 0.5 between pre- and post-test (R-sq = 25%), alpha = 0.05, power = 0.80 and minimum Cohen’s *d* = 0.60, at least *N* = 68 patients are required to reject the null hypothesis. With an estimated intra-class correlation (ICC) = 0.05 (adjustment for similarities that occur between patients due to sharing of a treatment group, cluster size = 6), which yields a design effect of 1.25 (1 + (6–1)*ICC), at least *N* = 85 participants are needed. Adding a safety margin of 20% dropout means a final sample estimate of *N* = 106 patients (*n* = 53 SleepWell, and *n* = 53 TAU).

### Recruitment {15}

Patients will be recruited from the Department of Pain Management, and Physical Medicine and Rehabilitation at the University Hospital of North Norway. These two departments evaluate and treat patients with persistent pain who frequently suffer from comorbid insomnia. Medical doctors, clinical psychologists, physiotherapists or nurses will orally inform about the SleepWell study and provide written study/registration information to eligible patients who accept an invitation to participate. Patients may also register via flyers/posters in the clinic waiting rooms. Patients will also be recruited from selected GPs in the city of Tromsø using the study’s inclusion and exclusion criteria. Based on experiences from previous group-based interventions at the same hospital departments, patient dropout is expected. Therefore, we recruit 1–2 extra patients to each study arm to ensure therapy group sizes of > 6 participants who finish.

### Methods: assignment of interventions

#### Sequence generation {16a}

The participants will be block-randomised with a variable block size of 4, 6 or 8 to maintain equal treatment and TAU group sizes and to conceal study arm allocation. The randomisation is performed using the “blockrand” library of RStudio with the following syntax: *randomisation* <—*blockrand*(*n* = *106*, *num.levels* = *2*, *levels* = *c(*“*SleepWell*”, “*TAU*”), *block.sizes* = *c*(*2*,*3*,*4*)) and *print*(*randomisation*).

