### Intervention descriptions {11a}

The group therapy format for the SleepWell intervention will consist of 6–8 patients in each group, led by two therapists, over seven sessions (~ 1.5 h per session). The first six sessions will be conducted weekly. Eight weeks thereafter, the seventh one is delivered as a consolidation session. The intervention follows a Norwegian group-based CBT-i manual for insomnia [62, 63], which is adapted for use on somatic patients. Between-session homework assignments are described in a corresponding paper workbook that is handed out during the first session. The treatment manual incorporates evidence-based therapeutic components commonly used in sleep intervention protocols [46, 47, 51]. The core components include behavioural procedures, i.e. stimulus control and sleep restriction—and cognitive and metacognitive strategies. Patients will also use implementation intentions [64] to change sleep-related habits.Part 1 introduces the treatment rationale and methods to achieve the intervention’s overall goals. Patients will be introduced to the self-report tools necessary for the daily self-monitoring assignments, which are expected to be completed between sessions. This module also includes psychoeducation on sleep physiology, causes of sleep problems, circadian rhythms and the rationale and practical usage of sleep diaries for recording sleep timing, continuity and duration.Part 2 focuses on establishing good sleep hygiene habits, introducing stimulus control and the practice of sleep restriction and the use of implementation intentions is introduced as a method for changing sleep-related habits.Part 3 addresses cognitive and meta-cognitive factors that maintain sleep disorders, and questions patients’ rationale for their attitudes and beliefs about the need for being occupied with sleep-related worry and rumination.Part 4 emphasises relapse prevention by integrating more functional sleeping habits into daily routines.

Table 1 summarises the main aims and contents/exercises across the four modules and seven sessions of the SleepWell intervention.

**Table 1 Tab1:** Overview of the SleepWell intervention [65, 66]

	**Main objective**	**Content and exercises**
**Part 1**	**Understanding sleep problems and assessment of sleep patterns**	

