#### Concealment mechanism {16b}

During the process of obtaining informed consent (item 26a), patients will undergo several assessments, including the collection of survey data via the www.nettskjema.no, a 2-day polysomnography/home sleep testing, and a 7-day sleep diary alongside actigraphy recording. Importantly, both research assistants and patients will remain blinded to the specific study arm to which each patient will be assigned. The principal investigator (PI) will generate the entire randomisation sequence using the above RStudio syntax and inform patients/assistants about the group assignment when at least 12, or preferably 16, patients have been included in the study. Knowledge of the group assignment remains concealed until participants have passed baseline assessments.

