### Trial status

The study recruits participants from January 2025 and estimates to complete the inclusion within December 2026.

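### The allocation list is fixed in advance by the investigator, its blocks are not aligned with the release waves, and the wait for a wave conflicts with the week-0 clock

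*Protocol article*

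**What the plan says.** Sequence generation {16a} describes a single list for 106 patients, made by one R call with random permuted blocks: "The participants will be block-randomised with a variable block size of 4, 6 or 8 to maintain equal treatment and TAU group sizes".

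Concealment mechanism {16b} says who makes it and when it is used: "The principal investigator (PI) will generate the entire randomisation sequence using the above RStudio syntax", and that person will "inform patients/assistants about the group assignment when at least 12, or preferably 16, patients have been included in the study". Before release, only research assistants and patients are described as unaware of the assignment. Baseline assessments are completed before disclosure.

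Three other places bear on this:

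- **Group size.** Intervention descriptions {11a}: "The group therapy format for the SleepWell intervention will consist of 6–8 patients in each group". Recruitment {15} adds one or two extra patients per arm to allow for dropout, and wants more than six to finish in each group.
- **Clock.** Participant timeline {13} calls baseline week 0, places the post-test at week 16, and says "The intervention group will begin the SleepWell programme immediately".
- **Accrual.** Trial status: "The study recruits participants from January 2025 and estimates to complete the inclusion within December 2026".

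**The concern.** Three things do not fit together.

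1. **Waves and blocks.** A therapy group starts when a wave is released. A list in random blocks of 4, 6 and 8 is cut wherever the wave ends, often inside a block, so a wave need not split evenly. At 12 or 16, only an exactly even split keeps both arms within 6 to 8.
2. **Knowledge of the list.** The R call produces every assignment at once. At the latest when the first wave is released, the person who ran it knows all later assignments. Variable block sizes protect against guessing by staff, not against the holder of the list.
3. **Time.** Baseline is taken as patients enter, but allocation waits until the wave is full. Week 0 and an immediate start cannot both hold for the early members of a wave.

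At stake are deliverable therapy groups, clean concealment, and a clock that means the same thing for every patient and both arms.

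**Working it through.** **Inputs from the article.** Block sizes 4, 6, 8; release at 12 or more, preferably 16; groups of 6 to 8; 106 patients from January 2025 to December 2026, about 24 months.

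**Assumptions.** Each block size is equally likely; each wave forms one therapy group per arm; accrual is even; baseline is taken at inclusion.

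**Do blocks end where waves end?** Let u(n) be the chance that a block ends at patient n, with u(0) = 1 and u(n) = [u(n−4) + u(n−6) + u(n−8)]/3. This gives u(12) = 10/27 = 37% and u(16) = 28/81 = 35%. Even the first wave therefore usually stops inside a block.

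**How often does a wave miss 6 to 8?** 30,000 simulated lists were cut into consecutive waves of a fixed size.

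| Wave size | Either arm outside 6–8 | SleepWell arm outside 6–8 |
|---|---|---|
| 12 | 41.6% | 20.8% |
| 13 | about 15% | about 8% |
| 14 | 3.6% | 3.6% |
| 15 | about 15% | about 8% |
| 16 | 40.8% | 20.5% |

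- Waves of 12: 6:6 in 58.4%, 5:7 in 37.8%, worse in 3.9%.
- Waves of 16: 8:8 in 59.2%, 7:9 in 37.2%, worse in 3.7%.
- At least one miss somewhere in the trial: 92% of lists (eight waves of 12) or 85% (six waves of 16).
- The first wave alone misses in 27%, because it starts on a block boundary.

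**Is arm balance harmed?** No. At 106 patients the arms differ by 0 in 73% of lists, by 2 in 27% and by 4 in 0.3%.

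**How long is the wait?** The accrual rate is 106/24 = 4.42 per month.

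| Wave size | Time to fill | First enrolee's wait | Mean wait | Patients waiting over 2 months |
|---|---|---|---|---|
| 12 | 12/4.42 = 2.7 months | 11/4.42 = 2.5 months | 1.2 months | 3 of 12 |
| 16 | 16/4.42 = 3.6 months | 15/4.42 = 3.4 months | 1.7 months | 7 of 16 |

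**What does the wait do to week 16?** At 4.35 weeks per month, the first enrolee waits about 10.8 or 14.8 weeks. A post-test 16 weeks after that patient's own baseline would fall 16 − 10.8 = 5.2, or 16 − 14.8 = 1.2, weeks after allocation. The sixth weekly session is 5 weeks after the first. The seventh follows 8 weeks later by Intervention descriptions {11a} (5 + 8 = 13 weeks after the first) or 4 to 6 weeks later by Table 1 (9 to 11 weeks). On either description the post-test would precede the last session. If week 16 runs from allocation instead, baseline is not week 0.

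**Crossover.** Participant timeline {13} times the TAU crossover from baseline. The blinding section {17a} times it from inclusion. Implementation {16c} describes a four-month waiting period that patients are told of at allocation. For the first member of a wave, the earliest and latest of these anchors can lie about 2.5 to 3.4 months apart.

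**The case against.** **The quoted aim is equal arms, and that is met.** This stands. A reader might infer that the blocks fail to balance the trial; the figures at 106 patients show otherwise. The defect is the size of therapy groups within a wave.

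**The 41% is the least favourable case.** Largely true. It needs waves of exactly 12 or 16, one group per arm per wave, and a miss in either arm. The article says at least 12, and a wave of 14 nearly always works. TAU groups form about four months later, after some attrition, so their count at allocation is not yet a group size. Yet 12 and 16 are the two sizes the article names, and TAU patients do go on to fill therapy groups.

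**The extra patients may absorb the misses.** Possibly, at 16. If Recruitment {15} means extras on top of 6 to 8, so that up to 10 may start, fewer than 0.1% of waves of 16 miss. The text does not say whether extras are counted inside 6 to 8. At 12 the extras do not help, since the miss is an arm of five. Even a 6:6 split of 12 cannot leave more than six finishers.

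**Choosing the cut-off does not change anyone's arm.** Correct. A reader might infer that the investigator could steer patients by closing at 12 or 16. With a fixed list followed in enrolment order, the cut-off changes when patients are told, not what they receive. An investigator who looked at the list could also find a workable cut-off in about 96% of waves or more (100% − 4% at 14 alone), though only by using advance knowledge. The remaining risk is influence over who is enrolled or in what order. The article has clinicians and general practitioners recruiting and does not say that the principal investigator enrols.

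**The wait does not bias the comparison.** It arises before disclosure and is equal across arms in expectation. A reader might infer a loss of power through a weaker pre-post correlation; the documents give no figure for how the correlation changes with time, so no size can be put on it.

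**Conclusion.** The point holds in limited form and merits a change for the waves still to be allocated.

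- **Group size:** block boundaries and release waves are not aligned. At exactly 12 or 16, about 41% of waves put an arm outside 6 to 8 (about 21% for the group that starts at once). The miss is nearly always one patient, and at 16 it may be covered by the planned extras. This rests on one group per arm per wave, which is inferred.
- **Concealment:** a full list known to the investigator is an avoidable risk, conditional on that person influencing enrolment or its order. No breach is shown.
- **Clock:** batched release contradicts the immediate start and the week-0 to week-16 schedule, and the crossover has three different anchors. That a wait exists follows from the text. Its length (up to about 2.5 to 3.4 months, mean 1.2 to 1.7) rests on even accrual and baseline at inclusion.

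Neither arm imbalance over the trial nor a quantified power loss follows from the documents.

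**What to change.** For every wave not yet allocated:

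1. Close the wave at an even size and lock its last baseline. Only then generate one 1:1 block of that size, recording seed and time. This fixes the starting split at 6:6, 7:7 or 8:8 and leaves no future assignments to know. Preferably someone not involved in enrolment runs it.
2. Count assessment weeks from the wave's allocation date in both arms.
3. Reconcile Participant timeline {13} (the immediate start, week 0 and the crossover from baseline), Implementation {16c} and the blinding section {17a} with the batched release in Concealment mechanism {16b}.
4. State whether the extra patients in Recruitment {15} fall inside or on top of 6 to 8, and reconcile its target of more than six finishers with a minimum wave of 12.

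The cost is one short R call per wave and an amendment of wording. Waves already allocated stay as they are. No added assessment is needed; repeating a questionnaire for only some patients would mix baseline timing and leave the other primary measures as they were.
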